## 7.5 Reporting procedures for serious adverse events

Events deemed as serious (see Section 7.3) must be reported to the investigator within 24 hours after the Investigator’s awareness of the SAE. This short time frame is in compliance with international regulations. All SAEs should be reported by the site staff in the CRF.

If the initial report is not complete, it should be followed by submission of a more detailed report within five calendar days.

All SAEs must be followed until resolution or until the Investigator assesses them as being under full control.

The reporting period for SAEs starts at capsule administration and ends at the final follow-up visit 6 months after end of IMP administration.

## 7.6 Reporting period for adverse events

All AEs, irrespective of nature, will be followed until resolution or until end of the follow-up period.

The reporting period for AEs starts at capsule administration and ends at the final follow-up visit 6 months after end of IMP administration.

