# 3. Cost benefit assessment

The risk posed to participants are primarily allergic reactions to the antibiotic used (clindamycin) and antibiotic associated diarrhoeal disease, particularly CDI, caused by clindamycin. Clindamycin is well tolerated and rarely causes allergic reactions and the optimal treatment of CDI is inoculation with healthy intestinal microbiota which half the study participants will receive and all can do in case CDI develops. Moreover, study participants are screened for *C. difficle* prior to study entry so the risk of CDI is very low. Inoculation with intestinal microbiota has in repeated trials been shown to be well tolerated and our clinical experience is also that this treatment is well tolerated. Should anyone accidentally bite the capsule this will be disgusting but not hazardous to health. Theoretically a participant might vomit and the inhale the contents of the capsules. This is likely to cause a severe pneumonia. However, participants are healthy volunteers and the number of tablets taken at each time point is small. The risk of aspiration pneumonia is therefore exceedingly small. The potential benefit of this treatment is to develop a rapidly available treatment for CDI and for prevention of CDI, a disease that causes considerable morbidity and mortality and for which current treatment regimens are either suboptimal or very cumbersome. The benefits therefore considerably outweigh the potential risks.

#

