# 7. SAFETY AND ADVERSE EVENTS

## 7.1 Specification of safety parameters

Safety parameters; Adverse drug reactions and serious adverse drug reactions and changes in vital signs.

Any apparent side effects experienced by the subject will be assessed from the time the subject signs the informed consent and throughout the course of the entire study, and will be reported by study site personnel either as a Baseline Event or an AE (6.2). The study personnel will document any Baseline Events or AEs in the CRF, whether observed by the Investigator or reported by the subject. The safety of the different treatment arms will be assessed with regard to AEs, baseline medical conditions, and findings from the physical examination and laboratory tests.

Possible adverse events will be elicited using a modification of the Common Terminology Criteria for Adverse Events version 3.0. as used by Youngster et al ([13](#_ENREF_13), [19](#_ENREF_19)). Fever, gastrointestinal symptoms, headache, fatigue, and rash will be the principle symptoms evaluated (appendix B).

The AE reporting period is described in Section 6.2.

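### AE and SAE reporting opens only at the first study capsule, so a serious clindamycin reaction in the preceding 9.5 or so days has no 24-hour reporting route

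*Protocol*

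**What the plan says.** Four parts of Protocol section 7 bear on when safety reporting starts.

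- **7.1** says that apparent side effects "will be assessed from the time the subject signs the informed consent and throughout the course of the entire study". Site staff enter them in the CRF as either a Baseline Event or an AE. For the period it adds: "The AE reporting period is described in Section 6.2".
- **7.2.1** defines an AE as occurring in a subject who has received the IMP.
- **7.5** says of serious events: "The reporting period for SAEs starts at capsule administration and ends at the final follow-up visit 6 months after end of IMP administration". The same section says that such events "must be reported to the investigator within 24 hours" of the Investigator becoming aware of them.
- **7.6** says of all AEs: "The reporting period for AEs starts at capsule administration and ends at the final follow-up visit 6 months after end of IMP administration".

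The schedule comes from elsewhere in the Protocol. Section 6.5 places randomisation at least an hour before clindamycin starts. Section 6.9 and Table 1 give every participant clindamycin on days 1-7, then a washout of two and a half days. The first supervised IMP or placebo dose falls on the third washout day, which is day 10. Section 3 lists allergy to clindamycin and clindamycin-associated diarrhoea, CDI above all, as the main risks to participants.

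**The concern.** The study itself imposes the antibiotic on healthy people, and the Protocol regards it as the main hazard. Yet the periods in 7.5 and 7.6 open after the antibiotic course has ended. A volunteer admitted to hospital with an allergic reaction on day 2 would meet the seriousness criteria in 7.3.1, but the event would fall outside the SAE period in 7.5. Section 7.1 reads as though such events are collected from consent, and its pointer to 6.2 leads to the study population, so it cannot settle which start applies.

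What is at stake is expedited notification of a serious event and its place in the final safety tables. Section 8.1 concludes that an independent monitoring board is unnecessary (although 6.6.1 and 7.8 still refer to a safety committee or board), which puts more weight on SAE reporting.

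**Working it through.** The Protocol gives no figure of its own on this point, so there is none to reproduce. The check sets the rules against the calendar.

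**Start of safety recording under each section**

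| Section | Starts at | Applies to |
| --- | --- | --- |
| 7.1 | Informed consent | Side effects, as Baseline Event or AE |
| 7.2.1 | Receipt of IMP | Definition of an AE |
| 7.3.1 | No start stated; IMP not required | Definition of an SAE |
| 7.5 | Capsule administration | SAE reporting period |
| 7.6 | Capsule administration | AE reporting period |

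Sections 7.2.1, 7.5 and 7.6 agree with one another. Section 7.1 starts earlier and relies on a category that the available text does not define.

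**Interval before the reporting period opens**

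- Clindamycin: 7 days (6.9). Washout: 2.5 days (6.9). Participants: 24 (6.1).
- Days from first clindamycin dose to first study capsule: 7 + 2.5 = 9.5, which agrees with day 10 in Table 1.
- Person-days on clindamycin: 24 x 7 = 168.
- Person-days after randomisation and before the period opens, counted from the first clindamycin dose: 24 x 9.5 = 228.
- Clindamycin doses per participant in the interval: 3 x 7 = 21, the complete course.

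**A serious reaction on day 2, taken through the rules**

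1. 7.3.1: it is an SAE if, for example, it requires admission.
2. 7.2.1: it is not an AE, because no IMP has been received.
3. 7.5: it precedes the SAE period, so the 24-hour rule does not reach it.
4. 7.1: it can be entered in the CRF as a Baseline Event. The AE grading for seriousness in 7.4 and the 24-hour route in 7.5 are not extended to that category.

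The event is therefore documented at most, and not reported as an SAE.

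**The case against.** The strongest defence is that the Protocol intends two tiers: Baseline Events from consent to the first study capsule, then AEs. On that reading 7.1 does not contradict 7.5 and 7.6, and pre-capsule events still reach the CRF. This stands in part. It shows that the events are not lost, but it does not give a serious one a reporting route.

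A second defence is that clindamycin is also taken as a capsule, so capsule administration might mean day 1. The wording does not favour this. The same sentences in 7.5 and 7.6 end by reference to the IMP, 6.9 separates clindamycin from the IMP or placebo dose, and 7.2.1 requires IMP. If the phrase is ambiguous, that is a further reason to reword it.

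A third is that a window opening at the study capsule suits a comparison of capsule safety. That is right for the between-arm analysis. It does not justify using the same window for safety reporting.

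Several stronger readings are tempting but not supported:

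- *No data exist for days 1-10.* Section 6.10 and Table 1 have CRF B completed daily from treatment start, so a pre-capsule record of symptoms exists.
- *Carry-over clindamycin symptoms bias the primary comparison.* Both arms take the same course after 1:1 randomisation and are followed alike under blinding. Carry-over is balanced in expectation and adds noise.
- *Clindamycin-associated CDI escapes reporting altogether.* Section 1 notes that CDI can arise weeks after antibiotics. A case starting after the first capsule is inside the period.
- *Some 60% of exposure is uncovered.* That figure (9/15) counts washout days as exposure. On dosing days alone it is 7/(7 + 5) = 58%, and reporting in any case continues for six months. The 9.5 days is the sounder measure.
- *The sponsor is cut out of SAE reporting.* The recipient in 7.5 is circular, but 7.7 delegates SADR and SUSAR reporting to the investigator while the sponsor keeps ultimate responsibility. The fault is unreconciled wording.

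**Conclusion.** The point holds as a gap in AE and SAE classification and reporting. For about 9.5 days per participant, 228 person-days over 24 volunteers, a serious clindamycin reaction meets the SAE definition but lies outside the SAE reporting period. That interval contains the entire antibiotic course, which section 3 treats as the main source of risk. The wording should be corrected, because following 7.5 as written leaves such an event without 24-hour notification.

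The conclusion rests on two readings: that capsule administration in 7.5 and 7.6 means the study capsule, and that Baseline Event has no definition elsewhere that carries a seriousness route. It does not depend on any event rate. It does not extend to a loss of symptom data, to bias between the arms, or to events that start after the first study capsule.

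**What to change.** 1. Reconcile 7.1, 7.2.1, 7.5 and 7.6 so that AE and SAE reporting starts at one point: consent, or at the latest the first clindamycin dose. Reword 7.2.1 so that receipt of IMP is no longer a condition. Define Baseline Event or remove it; if it is kept, state that serious events in that category follow the SAE route.
2. Tabulate pre-capsule events separately from those that are new or worse after the first study capsule, using the CRF B entries already planned as the reference. The between-arm capsule comparison then keeps its own window. The details can sit in the SAP.
3. Correct both references to 6.2 in section 7.1 so that they point to 7.6.
4. Reconcile the SAE recipient in 7.5 with the delegation in 7.7 and with 6.6.1, which expects the sponsor to unblind a reportable case, so that it is clear who notifies whom.

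The cost is a protocol wording amendment and a few more events to report. No new visit or form is needed, since CRF B already runs from day 1.

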## 7.7 Sponsor’s reporting of serious adverse drug reactions and suspected unexpected serious adverse events

The Investigator and /or Bactavia or designee have to make a causality (relationship) assessment. The term SADR (Serious Adverse Drug Reaction) is to be used when the Investigator deems the SAE as possibly or probably related to the IMP. Serious Adverse Drug Reactions are to be reported annually to the MPA and the ethical committee.

If the event is not described before, e.g*.* in the IB, the event is a SUSAR (Suspected Unexpected Serious Adverse Event). Bactavia or designee has the obligation to submit SUSAR reports electronically to the Eudravigilance database within:

- 7 days if fatal or life-threatening (follow-up information within an additional 8 days)
- 15 days if non-fatal and non-life-threatening (follow-up information as soon as possible)

The following bodies are recipients of the reports, and procedures for such reports are familiar to investigator or designee:

- MPA
- European Medicines Agency (EMA)
- The study approving IEC

Bactavia has delegated the task of reporting SADR/SUSARs to the investigator, but has the ultimate responsibility for the fulfilment of these tasks. This delegation is enforced in a written delegation.

Bactavia also has the obligation to, once a year throughout the clinical study (or on request); submit a safety report to the MPA and the IEC taking into account all new available safety information received during the reporting period.

## 7.8 Stopping rules

If an attending physician assesses that a patient is suffering from an adverse event induced by the IMP and requiring treatment, IMP treatment will be stopped for that patient. The outcome will be classified as an adverse event necessitating treatment stop. Should a study participant develop CDI this will be treated as per routine with metronidazole and in case of recurrence with autologous faecal transplant as per routine.

The data and safety monitoring board and the Swedish Medical Products Agency have the right to stop the study.

A study subject can terminate his/her participation in the study at any time without giving a reason why as outlined in patient information (appendix C). Should a subject wish to do so he/she will be treated in line with standard recommendations.

Study organisers can end a patient’s participation for safety reasons.

If a patient is excluded, already collected data will be used in subsequent analyses unless he/she objects.

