# 5. Outcomes

## 5.1 Primary endpoint

The safety and tolerability of oral, capsulized, previously frozen, autologous faecal microbiota transplantation up to 21 days after the end of faecal treatment in healthy volunteers.

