## 11.3 Data analysis

Final analysis will include a description of included participants, proportions of adverse events and any serious adverse events, the proportion of participants withdrawn or lost to follow up. Categorical variables will be compared between patient groups using the χ^2^ test or Fisher exact test and continuous variables using quantile regression.

For microbiota Shannon indexes for diversity will be calculated in all samples and tested for significance with Wilcoxon rank-sum test. Using the QIIME pipeline, unweighted UniFrac distances are then produced and used for investigation of beta diversity through plotting PCA coordinates

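### Section 7.8 lets an excluded participant's objection take recorded adverse events out of the primary safety analysis, so removal can depend on the outcome

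*Protocol*

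**What the plan says.** The rule is one sentence at the end of Protocol section 7.8: "If a patient is excluded, already collected data will be used in subsequent analyses unless he/she objects". The sentence just before it reads: "Study organisers can end a patient’s participation for safety reasons". A participant removed because of a safety event is therefore among those to whom the rule applies.

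The same section treats two other situations separately. When an adverse event attributed to the study product needs treatment, the product is stopped, and "The outcome will be classified as an adverse event necessitating treatment stop". Voluntary departure is also covered: "A study subject can terminate his/her participation in the study at any time without giving a reason why". Section 7.8 does not define exclusion or say whether voluntary departure counts as exclusion. Section 6.7, on subject withdrawal, lists reasons for discontinuation but is silent on data already collected.

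The primary endpoint in 5.1 is "The safety and tolerability of oral, capsulized, previously frozen, autologous faecal microbiota transplantation up to 21 days after the end of faecal treatment". Section 11.3 plans to report "proportions of adverse events and any serious adverse events, the proportion of participants withdrawn or lost to follow up", and adds: "Categorical variables will be compared between patient groups using the χ^2^ test or Fisher exact test". Section 11.1 sets 12 participants per arm and states that no power calculation was done.

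**The concern.** The analyses from which data may be left out are not qualified, so they include the primary one. Nothing in the protocol exempts adverse events, exposure or the reason for leaving.

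Both steps that lead to removal can be related to a bad experience: being excluded, possibly for safety, and then objecting. Blinding does not break that link, because a participant reacts to symptoms whether or not the allocation is known. The participants whose data may disappear from the safety tables can thus be the ones the safety tables exist to count. With 12 per arm, one such participant can decide whether an arm is reported as free of a given event.

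**Working it through.** The protocol has no figure to reproduce here. The check is to read the clauses together and then size the consequence.

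**Reading the clauses together**

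1. Section 7.8: exclusion may be for safety reasons.
2. Section 7.8: after exclusion, recorded data are used by default, but not if the participant objects.
3. Sections 5.1 and 11.3: the primary endpoint is safety, reported as proportions with adverse events.
4. No section exempts safety data from step 2.

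It follows that an objection by someone excluded after an event takes that event out of the numerator and the person out of the denominator.

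**Inputs for the sizing**

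- From the documents: n = 12 per arm (11.1).
- Assumed: the event counts, the number of objectors and the 10% event rate used below. The protocol gives none of these.
- Chosen here: exact (Clopper-Pearson) two-sided 95% limits. With zero events the upper limit is 1 − 0.025^(1/n). With one event it is the p that solves (1 − p)^n + n·p·(1 − p)^(n−1) = 0.025.

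**Active arm, when each objector had an event**

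| All data kept | 95% limits | Objectors | Reported | 95% limits |
|---|---|---|---|---|
| 1/12 = 8.3% | 0.2% to 38.5% | 1 | 0/11 = 0% | 0% to 28.5% |
| 2/12 = 16.7% | 2.1% to 48.4% | 1 | 1/11 = 9.1% | 0.2% to 41.3% |
| 2/12 = 16.7% | 2.1% to 48.4% | 2 | 0/10 = 0% | 0% to 30.8% |

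For example, the upper limit for 0/11 is 1 − 0.025^(1/11) = 0.285.

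**Direction in the comparison.** Suppose each arm has one event in 12, so the true observed difference (active minus placebo) is 0.

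- Active-arm participant with the event objects: 0/11 − 1/12 = −8.3 percentage points, so the capsules look safer.
- Placebo participant with the event objects: 1/12 − 0/11 = +8.3 percentage points, so the capsules look worse.

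An objector without an event moves the arm's rate slightly upwards: 1/12 = 8.3% becomes 1/11 = 9.1%.

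**Contrast with loss unrelated to outcome.** The chance of seeing at least one event is 1 − (1 − p)^n. At an assumed p of 10% it is 1 − 0.9^12 = 71.8% with 12 participants and 1 − 0.9^11 = 68.6% with 11. Losing one participant at random costs little. The damage comes from losing the participant who had the event.

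**The case against.** The strongest reply is that the clause is narrow. The default is to use the data, and removal needs both exclusion and an active objection. Stopping the study product for an adverse event is not itself exclusion and is kept as a classified outcome. Section 6.7 asks investigators to make every reasonable effort to keep subjects in the study. The objector counts above are hypothetical, and appendix C, which may say more about participants' data, is not shown. All of this stands, and it makes the event less likely. It does not supply the missing exception.

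A reader might also infer more than the text supports:

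- **That records are deleted.** The clause governs use in analysis. Sections 7.4 and 7.5 still require events to be recorded, and 8.8 keeps source documents for 10 years.
- **That 7.8 contradicts 7.7.** The annual report in 7.7 is to be written "taking into account all new available safety information received during the reporting period". That is a regulatory duty, and both sections can be followed at once. An event could appear in that report and not in the final analysis, which is a consequence to avoid but not a contradiction.
- **That the removal is invisible.** Section 11.3 still counts withdrawals, so the departure would show. The event behind it need not.
- **That the bias always favours the capsules.** Both arms take clindamycin, so placebo participants can have events and object too. The direction depends on the arm and on whether the objector had an event.

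Finally, one could leave the matter to a statistical analysis plan. The protocol does not leave it open, however. It fixes the rule, and an analysis plan could not properly restore data that the protocol lets a participant withhold.

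**Conclusion.** The point holds in this form: section 7.8, as written, permits removal of recorded safety data that depends on the outcome, in a trial whose primary endpoint is safety. In the simplest case, 1/12 with an upper limit of 38.5% becomes 0/11 with an upper limit of 28.5%. With two objectors, 2/12 (upper limit 48.4%) becomes 0/10 (30.8%). These sizes assume that the objectors are in the active arm and are the participants with events. How often that would happen cannot be derived from the protocol.

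This is a rule worth correcting because the correction is cheap. It does not show that the safety analysis will be biased, and the documents do not support a charge of erased records or of conflict with regulatory reporting.

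**What to change.** Revise the last sentence of section 7.8 to state that:

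- adverse events, capsule exposure and the reason for leaving, as recorded up to exclusion or withdrawal, stay in the safety analysis;
- an objection stops further collection of data and further use of stored samples;
- exclusion does, or does not, cover voluntary withdrawal, with section 6.7 brought into line.

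Put the same wording in the participant information (appendix C), subject to ethics approval. Add to section 11.3 that the number of participants whose data are nevertheless left out is reported by arm, with the reason.

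The cost is about a sentence in each place, made before enrolment. The downside is that participants give up the option of having recorded safety data left out of the analysis, and this must be stated plainly at consent.

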# 8. STUDY MANAGEMENT

## 8.1 INDEPENDENT DATA SAFETY MONITORING BOARD (DSMB)

An independent Data Safety and Monitoring Board is required if a study poses a considerable risk to study participants and if the study duration is long and divided into blinded and nonblinded groups. Oral capsules with faecal bacteria from healthy donors have been shown to be safe and well tolerated in several clinical trials ([13](#_ENREF_13), [20](#_ENREF_20), [21](#_ENREF_21)). We are using the same study capsule as in previous studies but with autologous faeces. Furthermore, the dosing protocol is two capsules twice daily for five days compared to 15 capsules once daily for two days in previous studies. If anything, this schedule is likely to result in fewer adverse events as intake of 15 capsules in one go is potentially difficult. The follow up is only 6 months and the healthy patients are studied. A data safety and monitoring board is therefore not necessary.

